### Design

The study uses a cluster-randomized, stepped-wedge controlled trial design. Randomization will occur at the commune level and communes will be assigned to receive either the SSM intervention first or the control condition first. The control condition will be enhanced treatment as usual. Those communes assigned to receive the control condition first will receive the SSM intervention 4 months later. This will ensure that the study is conducted ethically and will not deny evidence-based services to members of the control group. Participants in the intervention and control groups will be from different communes, or municipal districts, meaning that they do not access the same service units. This will minimize the risk of contamination. Figure 2 shows how the design will operate. The *black rows* depict the experimental data collection periods, *diagonally striped rows* are the control data collection periods, and the *gray rows* represent the long-term data collection period. The primary measure of interest is the proportion of individuals in the experimental versus the control group (*black* versus *diagonal striped*) that went from being a case of depression (SRQ-20 > 7) to being non-case (SRQ-20 < 8) over the experimental data collection period. Based on the feasibility case rate of a mean of one case every 14 days, each commune is expected to have eight completed cases (baseline, month-1 and month-2 measures) per year for a total *n* of 256 cases. Figure 3 shows a SPIRIT figure depicting the study design. Additional file 1 provides an overview of the elements of the study protocol, as described in a SPIRIT checklist.  Recruitment will continue until the desired sample size is reached and data can be analyzed to assess the effectiveness of the intervention.

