### Power calculation

The number of subjects required for this randomized cluster trial was calculated by estimating the number that would be required in a completely randomized design and then adjusting this number by the design factor associated with a randomized cluster trial (Table 2). The number of subjects required for a completely randomized design was calculated by the R function pwr.t.test [29] using the following characteristics:An effect size of 0.5 (where a small effect size is 0.2; medium is 0.5; large is 0.8)Significance level – type 1 error rate (0.05)a two-sample design

Using a medium effect size (0.5) results in an estimate of 64 subjects per arm or 128 in total at an 80% power.

**Table 2 Tab2:** Sensitivity analysis

Effect size	ICC	Number per cluster	Total *N* required
0.5	0.05	8	173
0.8	0.05	8	69
0.2	0.05	8	1063
0.3	0.05	8	474
0.4	0.05	8	268
0.45	0.05	8	212
0.5	0.025	8	150
0.5	0.01	8	132
0.5	0.005	8	132
0.45	0.005	8	163

*ICC* intracluster correlation coefficient

The Design Effect (DE) is estimated by the formula:$$ D E = 1 + \left(\mathrm{n} - 1\right) \times \mathrm{p} $$where

*DE* = Design Effect

*n* = number of subjects in each cluster

*p* = ICC (intracluster correlation coefficient)

No estimates of the SRQ-20 intracluster correlation coefficient (ICC) are available; however, within the research literature on estimating sample sizes, the ICC is usually described as small with values of 0.01 to 0.05 – with a median of around 0.01. We have used the upper value of 0.05. This is the number of participants who will be found to have an SRQ-20 > 7 and will be followed up over the 2 months. This was estimated from the feasibility data, which produced approximately one subject every 14 days within primary care centres (or one every 2 weeks). We therefore estimate a mean of eight subjects per commune would be completed in the experimental or control time period, meaning that the total *n* during the study period is 32 clusters × 8 completed subjects per cluster or 256 subjects. The DE associated with eight subjects per cluster, a medium effect size of 0.05, and an ICC of 0.05 is 1.35, meaning that the randomized cluster study requires 128 × 1.35 or 173 subjects which is below the anticipated *n* of 256.

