There are three outcome variables being collected from each client in the study: SRQ-20, WHODAS 2.0 and CAGE. The SRQ-20 can be used as individual scores as well as primary of reporting the clients with scores either >7 or <8 to compute a rate for non-case as a proportion, and can be used as the entire interval of scores that are ordinal and so allow for ordinal statistics to be described as well as modeled. The WHODAS 2.0 and CAGE will be analyzed in the form they are scored, with no collapsing to subcategories unless later modeling justifies this. The SAP will describe what might be done in various circumstances.

Since the design of this study is a clustered stepped-wedge design, the descriptive statistics will be displayed in the order of the commune implementation in the wedging: first or second; 3-month intervals over the study; time of observation: baseline, month 1 and month 2, and combining the commune data to up to the district, combining districts up to provinces and finally combining the provinces to the entire country of Vietnam (see Fig. 2). These descriptive statistics will include those listed above: sample size, minimum, median, maximum, lower and upper quartiles, mean, standard deviation and interquartile range, with plots (raw distributions as well as box plots) of the variables by what will be considered as factors: commune, district, province, country, order of implementation and timing of the measurements within each commune. Patterns will be noted to be justified with the statistical analyses conducted later. One type of pattern from the descriptive statistics is to do LOESS smoothing to suggest patterns versus time and the timing may suggest some relationships with time, such as skill of staff within commune or order during the entire trial, that need to be considered in the modeling, as these could impact the assumptions of the stepped-wedge analysis.

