Overall, the primary analysis will consider the proportions of non-caseness with the SRQ-20 within commune as the response variable using logistic regression assuming a binomial response distribution as part of the glm (generalized linear model) command in R [32]. The independent variables will be the cluster (commune), order of administration, and baseline value of the response variable, and then timing of the response at months 1 and 2. If the assumptions of the binomial data are not met, then a Poisson or negative-binomial model will be considered next, as they are known to model data better than the binomial. Standard assumptions, such as residual plotting, distributions of the residuals, influence and variance inflation, are checked to see how the models are impacted with the observations for possible deletion and remodeling. Differences between the models will be detected using AIC (Akaike Information Criterion), with smaller values detecting the better models. If some models are very close to each other, these will also be reported. Models that include higher levels of the combined communes as districts, provinces and the entire country will also be explored to gain further insight as the meaning the results. Finally, the raw scores from the SRQ-20 within commune will also be modeled, but differences between this model and the proportions model will defer to the proportions model as it was prespecified as the primary outcome variable in this protocol. In the design, we did not have a study-specific measure of the IC (intraclass correlation), we will estimate it for the four ways of doing the analysis so that future studies can use these estimates in their planning. Results will reported with *p* values in comparison with an alpha value of 0.05, and no correction for multiplicity. In addition, 95% CIs (confidence intervals) will be displayed for the results to make it easier for readers to decide whether the results are clinically important as well as their statistical significance with *p* values. Similar models and methodology will be used with WHODAS 2.0 and CAGE outcome variables. Reports will include all these analyses and any deviations will follow the SAP process for reporting. It is also possible to report all proportions as percentages for a suitable audience to understand.

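### The sample-size formula powers a between-commune comparison, but the stated primary model puts commune in as a glm term and removes that comparison; the two must be aligned and power restated

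*Protocol article*

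**What the plan says.** **Design.** The Design section states: "The study uses a cluster-randomized, stepped-wedge controlled trial design". There are two sequences: SSM first, or control first and SSM later. "Those communes assigned to receive the control condition first will receive the SSM intervention 4 months later". The primary comparison is described as follows: "The primary measure of interest is the proportion of individuals in the experimental versus the control group (*black* versus *diagonal striped". Long-term data collection is shown separately in Figure 2, which is not available here.

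**Sample size.** The Power calculation section starts from an individually randomized two-sample t-test: "Using a medium effect size (0.5) results in an estimate of 64 subjects per arm or 128 in total at an 80% power". It inflates this by 1 + (n − 1) × ICC, with n = 8 and ICC = 0.05, and concludes: "meaning that the randomized cluster study requires 128 × 1.35 or 173 subjects which is below the anticipated *n* of 256". Nothing in that section refers to a period effect, the crossover, or adjustment for commune.

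**Analysis.** The Analysis section again relies on the design ("Since the design of this study is a clustered stepped-wedge design") and says that time patterns may have to be considered in the modelling. The primary model is a logistic regression fitted with R's glm command. "The independent variables will be the cluster (commune), order of administration, and baseline value of the response variable", followed by the month of measurement. The list has no calendar-period term and no term for the commune's current condition (SSM or control).

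**The concern.** The factor 1 + (n − 1) × ICC belongs to a parallel cluster trial in which each commune sits in one arm and the arms are compared between communes. R's glm has no random effects, so commune as a predictor is a set of fixed effects. These absorb every difference between communes, including the randomized one. The power statement and the primary model therefore describe different comparisons.

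Two things are at stake. On one reading, the model as listed cannot produce the trial's main estimate. On the other, readers are told that 256 comfortably exceeds the requirement when the protocol has not shown this for the analysis it describes. A null result could then be read as coming from an adequately powered trial. The point is separate from the use of a t-test effect size for a binary outcome, and would remain if the outcome were the continuous score.

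**Working it through.** **Inputs from the protocol:** effect 0.5 SD; alpha 0.05 (sidedness is not stated, but two-sided reproduces 64 per arm); ICC 0.05; 32 communes; 8 subjects per commune; N = 256.

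**Assumptions:** 16 communes per sequence, equal commune sizes, total variance 1, normal approximation, and an SSM/control term added so that the effect can be estimated. For the two-period calculations the sequences are SSM–SSM and control–SSM with two equal periods.

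**1. The plan's own figure.** The t-test needs 63.8, so 64 per arm, or 128. The factor is 1 + 7 × 0.05 = 1.35, and 128 × 1.35 = 172.8, so 173. It reproduces. By the same formula 256 / 1.35 = 189.6 effective subjects, or 94.8 per arm, which gives 93% power at 0.5 and 78% at 0.4.

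**2. First period only.** Each commune has one condition. The 32 commune effects already use rank 32, and adding order of administration leaves the rank at 32. Order is fully aliased with commune, so the SSM effect is not estimable in the listed model.

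**3. Both periods.** Let m be the cases per commune-period, v = 0.95/m and τ = 0.05. Variance of the SSM effect:

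- fixed commune + period: v/4
- fixed commune, no period: v/8
- random commune + period: 1 / [4/v + 4/(v + 2τ)]
- random commune, no period: 1 / [8/v + 4/(v + 2τ)]

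Power is Φ(0.5/SE − 1.96). For example, with m = 4, v = 0.2375. Fixed + period gives SE = √0.0594 = 0.2437 and power 54%. Random + period gives 1/(16.84 + 11.85) = 0.0349, SE = 0.1867 and power 76%.

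| Model | N = 173 (m = 2.70) | N = 256 (m = 4) | N = 512 (m = 8) |
|---|---|---|---|
| Fixed + period | 39% | 54% | 83% |
| Random + period | 61% | 76% | 95% |
| Fixed, no period | 66% | 83% | 98% |
| Random, no period | 80% | 92% | >99% |

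**4. Accrual over a year.** The Design section gives eight completed cases per commune per year, with the switch at 4 months. Take three 4-month periods with 8/3 cases each, so v = 0.95/(8/3) = 0.356. Fixed + period has variance 3v/16 = 0.0668, SE 0.2585 and power 49%. Random + period has SE 0.2223 and power 61%.

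**5. Sensitivity.** With ICC 0.01 and N = 256 over two periods, the four models give 52%, 80%, 81% and 93% in the table's order. Letting the commune effect change between periods (autocorrelation 0.8) lowers power by at most about 3 points.

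**The case against.** The strongest defence is that the primary contrast is in effect parallel. The Power calculation section counts eight subjects per commune in the experimental or control period. One case every 14 days yields about 8.7 in 4 months, which matches the length of the control phase. The early communes' later months may belong to the separate long-term period and so fall outside the contrast. On this reading 1.35 is the correct factor, 173 is correct, and 256 gives about 93%. This stands as a defence of the sample size. It does not rescue the plan, because under this same reading the listed model cannot estimate the SSM effect.

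A second defence is that the low figures depend on choices the protocol does not make. Four cases per commune-period is stated nowhere, and the listed model has no period term. The year-long accrual rests on the eight-per-year statement, which conflicts with one case every 14 days (365/14, about 26 per year) in the same sentence. This also stands. A reader might infer from the 54% or 76% that 256 falls short of 80% at 0.5. The documents do not establish that: without a period term, with eight cases in each commune-period, or as a parallel comparison, power exceeds 80%.

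A third defence is that modelling detail is deferred to the SAP. Detail may be, but the protocol itself fixes the command and the predictors, and these do not match its own power calculation.

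**Conclusion.** The mismatch is real and holds under either reading, though its consequence differs.

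- **First period only:** the sample size is sound (80% at 173, about 93% at 256), and the stated model fails.
- **Both periods:** 80% at 173 is unsupported. It is reached only with random communes and no period term, which is not the stated model. Power at 256 is undetermined: 54% to 92% with 4 cases per commune-period, and 49% or 61% with period terms if accrual takes a year. Eight cases in each commune-period would mean 512 subjects and gives 83% or 95% with period terms.

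A reader might also infer that 173 is a wrong number. It is arithmetically right for its inputs and right for a first-period contrast; what is missing is an analysis to which it applies. These figures rest on a standardized continuous outcome, equal commune sizes and the assumed two-sequence layout, since Figure 2 could not be seen.

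**What to change.** 1. **Analysis section.** Replace commune as a glm predictor with a random commune intercept in a mixed logistic model, and include an explicit SSM/control term. If both periods enter the primary analysis, add calendar period.
2. **Design and Power calculation sections.** State which periods enter the primary contrast and how many cases each commune-period is expected to yield, and reconcile the per-year and per-period counts. Then restate power for that model:
   - if the contrast is first-period only, keep 1 + (n − 1) × ICC and quote the N completed in that period;
   - otherwise, use a two-sequence stepped-wedge calculation, revise Table 2 to match, and withdraw 173.

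The cost is a recalculation and some rewording; the change itself calls for no extra patients. The stated power may become less favourable, and a random commune effect adds a distributional assumption. In return, with 256 over two equal periods, moving from fixed to random commune effects with a period term raises power from 54% to 76%.

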If the expected effect size is under 0.45 the study is likely underpowered. In the feasibility study, nine of the 68 (13%) subjects remained at 8 or higher in the second SRQ-20 – thus, 87% dropped below 8, a very large effect of the intervention. While the effect size in the pilot study would fall into the “large” category the variable follow-up time makes the estimate suspect, and thus we used a medium effect size to account for the expected impact over a 2-month period. Based on the feasibility results of eight patients per cluster, an expected minimum effect size of 0.4, an ICC of no more than 0.05 the proposed study would be powered at approximately 80% with a 0.05 alpha level.

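### The power figure is calculated for a difference in mean scores, not for the primary non-case proportion, and the 0.4 and 0.45 statements conflict

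*Protocol article*

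**What the plan says.** The Power calculation section sizes the trial in two steps. First, "The number of subjects required for a completely randomized design was calculated by the R function pwr.t.test", with effect sizes graded 0.2, 0.5 and 0.8 as small, medium and large. "Using a medium effect size (0.5) results in an estimate of 64 subjects per arm or 128 in total at an 80% power". Second, the total is multiplied by the design effect 1 + (n - 1) × ICC, with 8 participants per cluster and an ICC of 0.05. This gives 173 against an expected 256 (32 communes of 8).

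Two statements follow within one paragraph. It opens with "If the expected effect size is under 0.45 the study is likely underpowered". It ends by saying that, at "an expected minimum effect size of 0.4, an ICC of no more than 0.05 the proposed study would be powered at approximately 80" per cent. Table 2 lists 268 participants for effect size 0.4 and 212 for 0.45, both at ICC 0.05.

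The Design section defines the outcome differently: "The primary measure of interest is the proportion of individuals in the experimental versus the control group" that changed from case (SRQ-20 above 7) to non-case (below 8). The Analysis section models this proportion by logistic regression. It adds that if the raw-score model and the proportions model differ, the proportions model prevails.

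**The concern.** The only power calculation supports the analysis that the protocol ranks second. A t-test on a standardised difference describes the raw SRQ-20 score; the primary test compares two proportions. Cutting a score at a threshold discards information, so a given shift in SD units generally has less power after the cut. Without a stated control or SSM non-case rate, a reader cannot tell which difference in proportions the trial can detect.

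The section also gives two answers on its own scale. An effect of 0.4 lies below 0.45, so the opening sentence makes the study likely underpowered at the minimum effect that the closing sentence calls adequately powered.

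At stake is how a null primary result is read. It would be set against a figure of about 80% that was never worked out for that outcome.

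**Working it through.** **Inputs from the protocol article.** Two-sample t-test, alpha 0.05, 80% power, 8 per cluster, 32 clusters, ICC 0.05, 256 completed participants. Sidedness is not stated; a two-sided test reproduces the 64 per arm. I take 1:1 allocation, so 128 per arm.

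**1. The protocol's own figures.**
- Design effect: 1 + 7 × 0.05 = 1.35.
- Effect 0.5: 128 × 1.35 = 172.8, stated 173.
- Effect 0.45: the t-test needs 78.49 per arm; 2 × 78.49 × 1.35 = 211.9, stated 212.
- Effect 0.4: the t-test needs 99.08 per arm; 2 × 99.08 × 1.35 = 267.5, stated 268.

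**2. Power at 256 by the same method.**
- Effective size per arm: 128 / 1.35 = 94.8.
- Effect 0.4: noncentrality 0.4 / √(2/94.8) = 2.754, power 78.2%.
- Effect 0.45: power 86.9%. Effect 0.5: power 92.9%.
- Smallest effect with 80% power: 0.409.

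So 0.4 falls 12 participants short of Table 2 (268 - 256), or about 4.5%. The boundary for 80% power is about 0.41, not 0.45.

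**3. Power on the primary outcome if 0.4 or 0.5 is an SD shift of the score.** Assumptions, none of them in the documents: normal scores cut at the caseness threshold, a control non-case rate p0 of 20-70%, and the ICC of 0.05 carried over to the binary outcome. Then p1 = Φ(Φ⁻¹(p0) + d). With n = 94.8 and p̄ the mean of p0 and p1:

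power = Φ[(p1 - p0 - 1.96 × se0) / se1], where se0 = √(2p̄(1 - p̄)/n) and se1 = √((p0(1 - p0) + p1(1 - p1))/n).

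Example, p0 = 0.50 and d = 0.4: p1 = 0.655, se0 = 0.0717, se1 = 0.0708, and power = Φ(0.21) = 58%.

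| Control non-case rate | SSM rate, d = 0.4 | Power | SSM rate, d = 0.5 | Power |
|---|---|---|---|---|
| 20% | 32.9% | 52% | 36.6% | 72% |
| 30% | 45.0% | 57% | 49.0% | 77% |
| 40% | 55.8% | 59% | 59.7% | 78% |
| 50% | 65.5% | 58% | 69.1% | 77% |
| 60% | 74.3% | 56% | 77.4% | 74% |
| 70% | 82.2% | 51% | 84.7% | 68% |

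On this reading, 80% power at d = 0.4 would need about 421 to 513 participants.

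**4. Power on the primary outcome if 0.4 is Cohen's h.** The pairs 50.6% vs 70% and 71.0% vs 87% both have h = 0.4. Power is 78.5% and 77.7%, almost the same as the t-test figure.

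**5. A difference the trial can detect.** For 50% vs 70%: se0 = √(2 × 0.6 × 0.4/94.8) = 0.0712, se1 = √(0.46/94.8) = 0.0697, and power = Φ[(0.20 - 0.1395)/0.0697] = Φ(0.87) = 81%.

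**6. Table 2, effect 0.5 with ICC 0.01.** The design effect is 1.07, and 128 × 1.07 = 137.0 (136.5 with unrounded n). The table shows 132, which is the value for ICC 0.005: 2 × 63.77 × 1.035 = 132.0. It appears in both rows.

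**The case against.** A reader might infer that the claimed power at 0.4 is simply not delivered. The documents do not support that. By the protocol's method it is 78.2%, which the word approximately covers, and 0.05 is stated as an upper limit for the ICC. At ICC 0.025 the power is 83.6%, and at 0.01, which the section gives as the literature median, it is 86.9%. Of the two conflicting sentences, the 0.45 one lies further from the arithmetic; it may simply reflect the next Table 2 row that fits within 256. This part of the objection stands in full.

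A reader might also infer that true power on the primary outcome is only 51-59%. That is not established either. It needs a normal score, an SD-shift reading of 0.4, and control rates that the protocol does not give. Under Cohen's h the loss almost disappears. The check also compares two proportions at one time point, whereas the planned model uses months 1 and 2 with a baseline covariate. The size of the loss is therefore conditional. Even so, the protocol names a t-test function and never mentions h, so the SD reading is the one its wording suggests.

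Finally, the trial is sized on 0.5, which needs only 173, and the uncontrolled pilot saw 87% fall below 8. If SSM reached 87%, power would be about 82% or more for any control rate up to 70%. This softens the consequence but leaves the mismatch in place. Nor is the mismatch a detail left to the SAP: the protocol fixes both the sizing method and the primary outcome, and the two do not agree.

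**Conclusion.** The concern holds in this form: the stated power was not computed for the primary outcome, and the section contradicts itself about 0.4 and 0.45.

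The mismatch of scale is the main point and rests on the text alone. Its size rests on assumptions: about 51-59% power at 0.4 and 68-78% at 0.5 under the SD-shift reading with control non-case rates of 20-70%, or about 78-79% at 0.4 under Cohen's h. On the SD-shift reading, even the base-case effect of 0.5 stays below 80% throughout that range.

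The internal conflict is certain but small in numbers: 268 against 256, 78% against about 80%, and a break-point of 0.41 against 0.45. The ICC 0.01 row is a table slip that changes no conclusion, since 132 and 137 are both far below 256.

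**What to change.** - Restate power for two proportions, with explicit control and SSM non-case rates and the design effect. For example, 256 participants at ICC 0.05 give about 80% power for 50% vs 70%.
- Reconcile the 0.45 and 0.4 sentences with Table 2: about 78% power at 0.4, and a minimum detectable effect of about 0.41. Label these figures as applying to the raw-score analysis.
- Correct the Table 2 row for effect 0.5 and ICC 0.01 from 132 to 137.

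The cost is text only, with no extra participants and no change to the analysis. The stated power may become less favourable. Recruitment is under way, but the article says that the SAP is still to be written, so the restated figures can be in place before the analysis.
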